## Aim and objectives

The general aim of the study is to investigate the potential health impacts of pesticides use on agricultural workers.

The specific objectives are:

To estimate the prevalence of high OPP and carbamate exposure via AChE concentrations found in agricultural workers’ capillary blood samples.To determine the proportion of workers with suboptimal behaviours that predict high exposure to pesticides.To examine workers’ health knowledge regarding pesticides-related risks, the prevalence of heath-protective behaviours, and self-reported ill health.To investigate possible associations between agricultural practices, health knowledge, health-protective practices and reports of ill-health, and the concentration of cholinesterase in capillary blood samples.

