#### Measuring blood cholinesterase concentrations in agricultural workers

Exposure to pesticides can be detected by low acetyl cholinesterase enzyme (AChE) concentrations in capillary blood samples. To measure AChE, we will utilise field kits containing lancets and reactive paper test strips (AChE field test kits, lot U620164, manufactured by the Government Pharmaceutical Organisation [GPO] Thailand). Blood samples (0.2 mL/capillary) will be obtained from a lancet-punctured fingertip of participants, undertaken by volunteer assistants drawn from public health officers, nurses, paramedics, or doctors in the local area. The samples will be allowed to precipitate for 30–45 minutes, followed by the reactive paper test. After 7 minutes, changes in colour on a paper test strip will be recorded using the four categories specified on the standard instruction sheet provided by the GPO with the test kits. The categories are: normal (AChE units per ml >100); safe (87.5–99.9); at risk (75.0–87.4); and probable health impact (<75). The outcome of primary interest is probable health impact.

The blood test results will be analysed alongside the interview data to determine whether participants with AChE levels that indicate probable health impact differ in their agricultural practices, health knowledge, health-protective practices and extent of self-reported illness. We will use descriptive and inferential statistics to explore associations (if any) between key variables, in line with specialist advice on appropriate multivariate analyses.

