#### Reporting

The data for each country will be reported separately to inform national stakeholders and policy makers. If the data are sufficiently similar across countries, we shall consider a combined analysis in a multilevel model. Otherwise, we shall undertake a meta-analysis to accommodate high heterogeneity.

We believe that abnormal AChE levels anywhere within our estimated range (28%-42%) will suffice as triggers to modify behaviour. Our models will identify behaviours that might usefully be targeted.

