### Predictors

2. Practices/Behaviours
Likely to increase exposureLikely to decrease exposure3. Knowledge

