### Analysis outline

Data will be summarised using appropriate descriptive statistics; we will report on associations between agricultural methods, health knowledge, health-protective practices, self-reported illness and blood test results.

Data from each country will be analysed separately before considering whether an analysis of pooled data is appropriate.

Description of all variables: frequencies, or ranges and measures of central tendencyCombining structured interview responses to give overall measures of: outcomes, knowledge, practices/behaviours and exposures. The variables to be combined will be listed *a priori*.Measures of ill-health, knowledge, behaviours and exposures will be described separately and together.Bivariate explorations will be used to examine the variables shown in Table 1.

**Table 1 pone.0258134.t001:** Contingency tables for each comparison.

	Ill-health measures	Exposure	Practices/behaviours	Knowledge	Cholinesterase concentration
Ill-health measures					
Exposure					
Practices/behaviour					
Knowledge					
Cholinesterase concentration					

4. Multivariate analysesPrimary outcomes: AChE concentrations, ill-health measures, separately & togetherCovariates to be tested one by oneCovariates with P<0.20 will be entered into exploratory models

a) Logistic regression: high AChE concentration, any ill-health, each health issue (modelling strategy to be based on backwards LR, -2LL, VIF, check enter model)

Predictors:

1. Behaviours
a. Likely to increase exposureb. Likely to decrease exposure2. Knowledge score3. Cholinesterase concentrations (when exploring ill-health)4. Significant covariates from one-by-one testing will include: location, SES, education, literacy (ability to write), age, gender, hours worked, distance between home and farm.

Sensitivity analyses will, in turn, exclude:

Migrant workersEarlier diagnosis of pesticide poisoning

A priori sub-group analyses:

Each countrySelf-employedLowest SES or income categoryNo formal education

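### Backwards LR elimination of the behaviour and knowledge terms is a poor basis for naming behaviours to target; the a priori measures should stay in every model and all be reported

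*Protocol article*

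**What the plan says.** All references are to the protocol article.

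- **Selection method.** Under Analysis outline, Multivariate analyses, the logistic models are for an AChE outcome and for "any ill-health, each health issue (modelling strategy to be based on backwards LR, -2LL, VIF, check enter model". This strategy is stated for the models as a whole. The predictors listed beneath it are behaviours likely to increase exposure, behaviours likely to decrease it, and a knowledge score. Covariates are screened one by one at P<0.20.
- **Outcomes.** The models cover AChE, any ill-health and each health issue, first in each country separately. A priori subgroups are also listed.
- **Composite measures.** Interview responses are combined into overall measures of knowledge and practices, and "The variables to be combined will be listed" in advance.
- **Use of the models.** The Reporting section states: "Our models will identify behaviours that might usefully be targeted". The Limitations section repeats this as the study's aim.
- **Main AChE category.** The section on measuring blood cholinesterase says: "The outcome of primary interest is probable health impact", meaning AChE below 75.
- **Objective 2.** Under Aim and objectives: "To determine the proportion of workers with suboptimal behaviours that predict high exposure to pesticides".

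**The concern.** The behaviour and knowledge terms are the quantities of interest, not nuisance covariates. Backwards elimination makes their presence in the result depend on the data. A term stays only if its estimate lies far enough from the null for its standard error, so retained odds ratios are exaggerated on average. Their intervals and P-values are then calculated as if the model had been fixed beforehand, and are too optimistic. The selected model holds no estimate for a dropped term, so a reader cannot tell a well-estimated null from an imprecise one.

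The procedure is repeated over outcomes and countries, and its results are meant for national stakeholders and policy makers. At stake is advice to farm workers that names some behaviours by chance, overstates others, and is silent about the rest.

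**Working it through.** **The plan's own figure.** Clustering gives a design effect of 1 + (120 − 1) × 0.01 = 2.19, with square root 1.48. Precision gives 35% prevalence with n = 360. The interval is 0.35 ± 1.96 × √(0.35 × 0.65 / 360) × 1.48 = 0.35 ± 0.073, or 27.7% to 42.3%. This reproduces the stated 28% to 42%. The protocol gives no error rate or cut-off for the regression models.

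**Inputs for the models.** From the protocol: three countries; at least two outcomes (AChE, any ill-health); three a priori measures (two behaviour scores and a knowledge score). Assumed: removal at 0.05, with 0.01 and 0.10 as the range; no true effect; independent tests.

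**Chance of at least one false predictor**, 1 − (1 − α)^tests:

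| Unit counted | Tests | α = 0.05 | α = 0.10 |
|---|---|---|---|
| One model | 3 | 14.3% | 27.1% |
| One country, two outcomes | 6 | 26.5% | 46.9% |
| AChE only, three countries | 9 | 37.0% | 61.3% |
| Three countries, two outcomes | 18 | 60.3% | 85.0% |

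At 0.01 the last row is 16.5%. With five health issues added (an assumed number), there are 3 × 7 × 3 = 63 tests, and the figure at 0.05 is 96.1%.

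**Check by simulation under the null.** Settings: three countries of 360, 35% AChE events, three predictors with correlation 0 or 0.4, eight null covariates screened at P<0.20, backward LR, 800 runs per setting. At 0.05 at least one term was falsely retained in 38% of runs for AChE only and 64–65% for AChE plus any ill-health. With five health issues added (20% each, latent correlation 0.4) it was 95%. The formula is therefore not misleading here.

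**If single items are entered.** A second null simulation took one AChE model with n = 360, independent binary predictors of 40% prevalence, Wald P standing in for LR, and 600 runs. At 0.05 at least one term was retained in 15.8% of runs with 3 terms, 41.8% with 10 and 66.5% with 20. At 0.10 the figures were 28.2%, 65.7% and 87.7%.

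**Size of the exaggeration, one illustration.** Take a binary predictor with 40% prevalence (assumed), n = 360, 35% events and no clustering. The standard error of the log odds ratio is about 1/√(360 × 0.35 × 0.65 × 0.4 × 0.6) = 1/√19.66 = 0.226. Retention at 0.05 needs |log OR| > 1.96 × 0.226 = 0.442, an estimate above about 1.56 or below about 0.64. A true odds ratio nearer to 1 than this can survive only if it is overestimated.

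**Room in the model.** Expected events per country are 0.35 × 360 = 126. Divided by the protocol's design effect this is 126 / 2.19 = 57.5, about 58. This is a rough guide, since a predictor that varies mainly within districts loses less.

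**The case against.** The strongest reply has five parts.

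1. **A rule is being read in.** No section says that survival alone identifies a behaviour. The plan adds a check against the enter model and speaks only of behaviours that might be targeted. *Partly stands.* The check is a real safeguard in the right direction, but elimination remains the stated strategy and these models are what identify behaviours.
2. **Cut-off and multiplicity method belong in an analysis plan.** *Stands.* Their absence is not the point. The point is the stated choice of backwards LR for the terms of interest.
3. **A reader might infer that a false target is more likely than not, or that most countries or outcomes would get one.** The documents do not support this as a general statement. The 60% needs 18 two-sided tests pooled over three countries that are reported separately, at an assumed 0.05. The combined measures and knowledge score favour the three-term reading, where a single model gives about 14%. If an association counted only in its expected direction, the 18-test figure falls further. Applied to the behaviour scores alone it is 1 − 0.975^12 × 0.95^6 = 46%; applied to all terms it is 1 − 0.975^18 = 37%. A pooled two-outcome analysis, which the plan may consider, gives 26.5%.
4. **A reader might infer that objective 2 would report the prevalence of chance findings.** No section says that its behaviours are chosen by elimination. The Predictors section classes them by expected direction.
5. **The survey is framed as exploratory and its size rests on prevalence precision.** *Stands as an argument against requiring family-wise control.* It does not justify elimination, because the models are put to practical use.

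The sentence on the outcome of primary interest can also be read as naming which AChE category matters, so it is not treated here as contradicting the list of primary outcomes.

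**Conclusion.** The point holds as a fault in a stated method. Backwards LR applied to the behaviour and knowledge terms gives exaggerated odds ratios, over-optimistic intervals and no estimate for dropped terms, in models meant to point to targets. With three a priori measures, the chance of at least one false predictor is about 14% per model, 27% per country with two outcomes, and 60% over three countries and two outcomes.

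These figures assume a 0.05 cut-off, no true effect and independent two-sided tests. They are higher at 0.10, with single items, or with each health issue added, and lower at 0.01 or if only AChE or a pooled analysis is used. The number of health issues and the cut-off are not in the document. The case for the change rests on the bias and incomplete reporting that elimination brings, not on any one of these percentages.

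**What to change.** In the Analysis outline, Multivariate analyses:

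1. Keep the a priori listed behaviour and knowledge measures in every model whatever their P-value, and do not apply backwards LR to them. This is the enter model that the plan already checks.
2. Base any statement about behaviours to target on those full-model estimates and confidence intervals, and report all of them.
3. Treat the AChE <75 models as the main basis for exposure-related targets. Label the per-health-issue and subgroup models exploratory, and state how many models were fitted.
4. Keep the number of terms modest, given about 126 expected events per country and about 58 after the design effect.
5. For objective 2, count the behaviours classed a priori, not those that reach significance.

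Formal multiplicity adjustment is optional.

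The cost is analysis wording only, with no new data. Intervals will be slightly wider and fewer behaviours will be singled out.

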#### Clustering

We will interview only one person from any one household to avoid data replications on household-level behaviours, such as laundry; this also allows us to use a single intra-cluster correlation coefficient (ICC) for responses from the same district. With no ICC available from our single-district Thai pilot study, we have used the unadjusted median ICC observed in primary care studies across a range of variables: (interquartile range [IQR] 0 to 0.032) [61], and set the ICC here to 0.01. With m = 120 interviews per district, our design effect, calculated as 1+(m-1)*ICC [62] is 2.19; this compares with design effects values ~1.5, as reported in surveys of developing countries [63]. Our confidence intervals are thus inflated by a multiplicative factor of 1.48 over those based on the assumption of independent responses; this adjustment accounts only for clustering within districts (groups of villages).

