#### Precision

We are testing the prevalence of cholinesterase concentrations likely to impact on health, estimated at 35% [59,60]. We are able to recruit 360 respondents in each country. We calculate that 360 respondents will allow us to verify this 35% prevalence, with 95% confidence intervals lying between 28% and 42%.

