## Fieldwork process

Sampling of cases is based on purposive sampling of three groups of villages/districts in each of the three countries and subsequent recruitment of agricultural workers. The three districts (or groups of villages) will be selected so that taken together they cover a range of small and large farms and spread of vegetable crop types.

Respondents will be sampled randomly from the population of farm workers in the village/district.

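### The country-level tests and logistic models make no allowance for district clustering; district should stay in every country model whatever its P value

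*Protocol article*

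**What the plan says.** Under Clustering, the protocol article takes district as the cluster and reports that it has "set the ICC here to 0.01", from a quoted interquartile range of 0 to 0.032. It continues: "With m = 120 interviews per district, our design effect, calculated as 1+(m-1)*ICC [62] is 2.19". The consequence is spelled out: "Our confidence intervals are thus inflated by a multiplicative factor of 1.48 over those based on the assumption of independent responses". The Precision section uses this factor to reach 28% to 42% around a 35% prevalence with 360 respondents per country.

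The Analysis outline puts separate country analyses first. It plans bivariate contingency tables (Table 1) and then logistic regression, with a "modelling strategy to be based on backwards LR, -2LL, VIF, check enter model". Covariates are screened singly and enter at P<0.20. District is one item under location in the Covariates list, and location is named among the significant covariates from that screening. No cluster term, robust variance or design-effect correction is given for the country models.

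A multilevel model does appear, but for pooled data and conditionally: "If the data are sufficiently similar across countries, we shall consider a combined analysis in a multilevel model". The Analysis outline repeats this for low or moderate heterogeneity between countries. Otherwise the country results are combined by meta-analysis.

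**The concern.** District is a feature of the sampling design. The protocol says it more than doubles the variance of a prevalence estimate, yet the country models seem to let a significance test decide whether it is accounted for. With three districts per country, a district difference large enough to distort other tests will often be too small to pass the screen. When district drops out, a predictor that happens to be commoner in a high-exposure district can pick up that district's difference.

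The country results go to national stakeholders, and the Reporting section says the models will identify behaviours to target. A false association at this stage could direct advice at the wrong practice. A meta-analysis of the country results would carry the same uncorrected standard errors forward.

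**Working it through.** **Inputs from the protocol article.** m = 120 per district, 3 districts and 360 respondents per country, prevalence 35%, ICC 0.01 with quoted range 0 to 0.032, entry screen P<0.20.

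**Assumed, because the article does not give them.** The share of a predictor's variance that lies between districts, and the backward-removal level (0.05 and 0.10 both tried).

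**1. The plan's own figures.**
- Design effect = 1 + 119 × 0.01 = 2.19; square root = 1.480.
- 95% CI = 0.35 ± 1.96 × 1.480 × √(0.35 × 0.65 / 360) = 0.35 ± 0.073, or 27.7% to 42.3%. This agrees with the stated 28% to 42%.

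**2. How often district fails the screen.** District has 2 df, and the P = 0.20 cut-off is 3.219. With the statistic inflated by the design effect (DE), P(fail) = 1 − exp(−3.219 / (2 × DE)).
- ICC 0.01: 1 − exp(−3.219 / 4.38) = 0.52.
- ICC 0.032: DE = 1 + 119 × 0.032 = 4.808; 1 − exp(−3.219 / 9.616) = 0.28.

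Simulation agrees: district passes in about 49% of runs at ICC 0.01 and about 72–75% at 0.032. At ICC 0.01 it survives backward elimination in only about 19–28% of runs (removal at 0.05) or 27–38% (removal at 0.10).

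**3. Type I error at nominal 5%.** Simulation used 3 districts of 120, a beta-binomial outcome at 35%, a predictor with no effect, and 3,000 runs (Monte Carlo standard error about 0.4 points at 5%). The ranges under planned selection cover the two removal levels.

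| Predictor variance between districts | ICC 0.01: district ignored | ICC 0.01: planned selection | ICC 0.01: district kept | ICC 0.032: district ignored | ICC 0.032: planned selection | ICC 0.032: district kept |
|---|---|---|---|---|---|---|
| 10% | 6.0% | 5.7–5.8% | 5.4% | 7.8% | 5.7% | 5.0% |
| 30% | 7.5% | 6.4–6.8% | 5.3% | 13.7% | 7.9–8.7% | 6.1% |
| 50% | 9.4% | 8.1–8.9% | 5.6% | 18.9% | 8.6–9.8% | 4.8% |
| 80% | 12.9% | 10.5–11.5% | 5.6% | 28.6% | 14.9–16.7% | 6.0% |

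A separate simulation at ICC 0.01 used a behaviour with prevalence 20%, 50% and 80% in the three districts. It gave 8.6% ignoring district, 7.0% under screen-then-eliminate, and 5.1% with district kept.

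**4. The limiting case.** For a predictor constant within district and tested without district, the rate is 2 × (1 − Φ(1.96 / √DE)).
- ICC 0.01: 1.96 / 1.480 = 1.324, giving 18.5% (simulated 18.2%).
- ICC 0.032: 1.96 / √4.808 = 0.894, giving 37.1% (simulated 36.9%).
- ICC 0: DE = 1, giving 5%.

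**The case against.** **Location may already be in the model.** The sentence naming location among the significant covariates can be read as a promise to include it. That is possible. But the sentence makes inclusion follow from significance in single-variable testing, and nothing exempts district from the later backward steps. Location also bundles district with type of area, farm type and crop, so a promise about location is not a promise about district.

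**Variance estimation belongs in an unseen analysis plan.** This would answer a complaint about silence. Here the article itself fixes the entry threshold and the selection method, and the fault lies in those rules as applied to district. The reference to specialist advice on multivariate methods, the label exploratory and the Limitations remark about significance levels do not alter them.

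**The plan's error rate is not 18%.** A reader might infer 18%, or 37%, from the design effect. The documents do not support that for the regression models, because district is at least a candidate there. Nor do the 52% and the 18% compound. If district fails the screen, its 2-df statistic is below 3.22, so a predictor nested in district cannot reach 3.84 on its own. Its single-variable false positives all arise where district has passed the screen. This objection stands.

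**Farm type and crop need not follow district lines.** A reader might infer that they do, because the districts are chosen so that "they cover a range of small and large farms and spread of vegetable crop types". That describes the three districts together, not one type per district. The Fieldwork process also has large or small farm recorded for each listed worker, which points to variation within districts. This too stands: no between-district share is given for any predictor.

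**The main predictors are behaviours and knowledge.** Where these vary mostly within district, the error stays near 5–6%, and the point does not apply to them.

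**Clustering is not ignored everywhere.** The conditional multilevel model for pooled data is a real provision. It does not reach the country analyses or a meta-analysis built on them.

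**Conclusion.** The point holds for the country-level tests and models, and for any meta-analysis that uses their standard errors. The protocol relies on district clustering for its prevalence interval and then, on the most natural reading, makes adjustment for it depend on a screen that misses a true district effect about half the time at the assumed ICC.

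The size is moderate. For predictors patterned strongly by district, type I error is about 7–12% at ICC 0.01 and 8–17% at 0.032, with no excess at ICC 0. These ranges depend on the assumed predictor patterns and removal level. The 18% and 37% figures belong only to a district-constant factor tested without district, which is what an unadjusted Table 1 comparison would do. The rule should be changed, because the correction is cheap and the country findings are meant to guide policy.

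**What to change.** - Keep the two district indicators in every country logistic model, exempt from the P<0.20 screen, any removal on VIF, and the backward steps. List district separately from the other location items.
- Carry these district-adjusted estimates and standard errors into any meta-analysis.
- Present the Table 1 tests as descriptive, or stratify them by district.
- Describe, and do not test, any factor that proves constant within district: three districts per country cannot separate it from district.
- In any pooled model, include district as well as country. Whether district is fixed or random is for the trial statistician, because nine district fixed effects would absorb the country contrasts that the Abstract promises.

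The cost is 2 degrees of freedom per country model, some rewording of the Analysis outline, and the loss of tests for factors that cannot be told apart from district. No extra data are needed. In the simulations, keeping district brought type I error to 5.1–5.6% at ICC 0.01 and 4.8–6.1% at ICC 0.032 for predictors that vary within district.

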## Abstract

Pesticides use in Southeast Asia has increased steadily, driven by the growth of large-scale commercial farming, as well as a desire to maximise food production in rural subsistence economies. Given that use of chemical pesticides, such as organophosphates and carbamates, has known potential health impacts, there are concerns about the safety of agricultural workers, and a need for a better evidence base to underpin regulation and worker education. This study, undertaken in 9 districts in Lao PDR, Thailand and Vietnam, will interview agricultural workers to investigate how they use pesticides, their knowledge of risks and self-protective practices, and their self-reported illness symptoms. In each district researchers will recruit and interview 120 participants engaged in vegetable farming, who have recently used pesticides, making a total of 1080 subjects divided equally between the three study countries. Workers’ degree of pesticides exposure will be determined from acetyl cholinesterase concentrations in capillary blood samples collected using field test kits, and these data will be analysed together with the interview findings. Country findings will be compared and contrasted, and general patterns noted. Knowledge gained about risky behaviours, self-protective practices and degree of association with serious pesticides exposure will assist policy makers and inform health improvement programmes.

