### Limitations

Because this study is a development project, it must be conducted with modest resources and a tight time schedule. This limits the scale and generalisability of the study. Other operational considerations include the need to proceed against the background of the COVID-19 pandemic, so that we must restrict data collection to accessible districts in a single province in each country. This means that we cannot use probability sampling for all levels of site and respondent selection, and affects the levels of statistical significance assumed in our analysis. As with all non-randomised studies, we cannot assume that association equates to causation. Rather, our aim is to identify behaviours predictive of adverse outcomes, and suggest strategies to target these behaviours.

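### No planned estimate of the knowledge association is adjusted for background confounders without also being adjusted for behaviour

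*Protocol article*

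**What the plan says.** The fourth objective (protocol article, Aim and objectives) is "To investigate possible associations between agricultural practices, health knowledge, health-protective practices and reports of ill-health, and the concentration of cholinesterase in capillary blood samples". The section on measuring blood cholinesterase likewise plans to compare health knowledge between participants with and without an AChE result in the worst category. The Abstract gives as motivation "a need for a better evidence base to underpin regulation and worker education".

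The Analysis outline sets two kinds of analysis for this:

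- **Crude.** "Bivariate explorations will be used to examine the variables shown in Table 1". That grid crosses ill-health, exposure, practices/behaviours, knowledge and cholinesterase with one another.
- **Multivariable.** Logistic models for AChE and for ill-health share one predictor list, which runs "Likely to increase exposureb. Likely to decrease exposure2. Knowledge score". Cholinesterase is added when ill-health is the outcome, followed by covariates that pass one-by-one testing. Selection is described as "modelling strategy to be based on backwards LR, -2LL, VIF, check enter model".

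No multivariable model containing knowledge without behaviours is named. Under Limitations, the authors decline to read association as causation and say that "our aim is to identify behaviours predictive of adverse outcomes, and suggest strategies to target these behaviours".

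**The concern.** What a worker knows about pesticide risk plausibly affects AChE in large part by changing what the worker does. Behaviour then lies on the path from knowledge to exposure. A model holding both terms splits the knowledge association and reports only the piece left after the measured behaviours are accounted for. Backward selection can then drop that piece. The check against the enter model does not recover the rest, because that model also contains the behaviours.

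The crude knowledge tables do not fill the gap. Education, SES and literacy can influence both knowledge and exposure, and the plan itself lists them as covariates. The reader will therefore have a knowledge association adjusted for nothing, or one adjusted for confounders and for behaviour together. The version most relevant to worker education, adjusted for background characteristics only, is not planned.

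**Working it through.** **The plan's own figure.** The article gives no figure for a knowledge effect. Its only related calculation is the precision statement (Clustering and Precision). With m = 120 per district and ICC 0.01, the design effect is 1 + 119 × 0.01 = 2.19, and √2.19 = 1.48. With n = 360 and p = 0.35, 0.35 ± 1.96 × √(0.35 × 0.65/360) × 1.48 gives 27.7% to 42.3%. This agrees with the stated 28% to 42%.

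**How much could the joint model attenuate the knowledge odds ratio?** This was examined by simulation.

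- From the article: n = 360 per country, prevalence about 35%.
- Assumed: knowledge K and behaviour B standardised, with correlation a = 0.3 or 0.5; total log-odds for knowledge ln(0.7) per SD; a share s of it running through behaviour, with s = 0, 0.5 or 1; two-sided 5% tests; independent responses; no covariates.
- Model: B = aK + √(1−a²)·e; logit P = −0.68 + (1−s)·ln(0.7)·K + [s·ln(0.7)/a]·B.
- Fits: K alone, then K with B. Odds ratios come from 400,000 records, detection rates from 600 samples of 360.

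| a | s | OR, K alone | OR, K with B | Detected, K alone | Detected, K with B | p < 0.10 for K, with B |
|---|---|---|---|---|---|---|
| 0.3 | 0 | 0.70 | 0.70 | 88% | 84% | 89% |
| 0.3 | 0.5 | 0.71 | 0.84 | 83% | 34% | 45% |
| 0.3 | 1 | 0.75 | 1.00 | 73% | 4% | 10% |
| 0.5 | 0 | 0.70 | 0.70 | 87% | 77% | 87% |
| 0.5 | 0.5 | 0.71 | 0.84 | 88% | 29% | 41% |
| 0.5 | 1 | 0.72 | 1.00 | 85% | 5% | 12% |

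The last column approximates retention under backward selection if terms were removed at p ≥ 0.10. The article states no removal threshold, so that is also an assumption. The a = 0.3, s = 1 row needs a very strong behaviour effect: ln(0.7)/0.3 = −1.19, an odds ratio of 0.30 per SD.

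**Error in the behaviour score.** Behaviour is self-reported, so B will not be measured perfectly. A second set of assumptions used full mediation and a behaviour odds ratio of 2 per SD, with total knowledge odds ratios of about 0.82 (a = 0.3) and 0.72 (a = 0.5). The joint-model knowledge odds ratios are then:

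- reliability 1: 1.00 and 1.00
- reliability 0.7: 0.94 and 0.89
- reliability 0.5: 0.90 and 0.82

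**Clustering.** The detection rates above assume independence. Dividing the standardised effect by 1.48 applies the whole design effect, which is an upper bound on the loss for a predictor that varies between individuals. A rate of 73% corresponds to 0.613 + 1.96 = 2.573; 2.573/1.48 = 1.739; Φ(1.739 − 1.96) = 41%. By the same steps 88% becomes 56%, 34% becomes 18% and 29% becomes 16%. All the power figures fall, and the contrast between the two models remains.

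**The case against.** The strongest reply is that the joint model is right for its purpose. The article says its models are meant to identify behaviours worth targeting, and it disclaims causation. Adjusting behaviours for knowledge is reasonable for that. Objective 4 asks for possible associations, not for a total causal effect of knowledge, and it does not specify adjustment. This stands, and it means the joint model should stay.

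A reader might infer that knowledge will come out with an odds ratio near 1, and that the report would then conclude that knowledge is unrelated to exposure and education is useless. The documents do not support this, for three reasons:

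- Table 1 covers knowledge by cholinesterase, knowledge by ill-health and knowledge by practices. Even under full mediation, readers would see a crude knowledge-AChE association, a knowledge-behaviour association and a behaviour odds ratio.
- An odds ratio of 1.00 needs the whole effect to run through behaviours that the interview measures without error. Nothing in the article says so, and partial mediation or measurement error leaves a residual association.
- Nowhere is the knowledge odds ratio named as the test of whether education works. Worker education appears as motivation for the study.

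It can also be said that a condensed article need not set out every modelling step, and that it defers to specialist advice on multivariate methods. That has some force. But the predictor list and the selection method are stated, and the point concerns what they deliver.

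**Conclusion.** The point holds as a gap in a stated analysis. The plan offers a crude knowledge association and one adjusted for confounders and behaviour together, with nothing between. If knowledge acts partly through behaviour, its adjusted odds ratio will understate its association with AChE and ill-health, and selection may remove it. Which behaviours survive selection also determines what the knowledge coefficient means, and this could differ between the countries, which are analysed separately first.

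The size is not fixed by the documents. Under the assumptions shown, a total odds ratio of about 0.70 to 0.75 per SD is unattenuated with no mediation, becomes about 0.84 with half, and 1.00 with full mediation and no measurement error. The mediated share, the knowledge-behaviour correlation, the effect size and the reliability of the behaviour score are all assumed. The prevalence objective and the behaviour odds ratios are not affected.

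**What to change.** For AChE and for each ill-health outcome, add one logistic model with the knowledge score and background covariates (district, age, gender, SES, education, literacy), without behaviours. In the ill-health models, leave cholinesterase out as well, since it lies downstream of behaviour. Keep knowledge in this model rather than exposing it to backward selection.

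Report this as the knowledge association, beside the joint model. Label the joint-model knowledge coefficient as conditional on measured behaviours. The behaviour odds ratios can remain adjusted for knowledge.

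The cost is one extra model per outcome and a sentence or two in the Analysis outline, with no new data.
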